**Figure 1 BMJOPEN2015010079F1:**
[figure not shown]
Schematic diagram of the schedule and time commitment for trial participants in each study group (CRN, Clinical Research Network; ES, electrical stimulation; NHS, National Health Service).

### Randomisation

Following baseline measures, participants will be randomised to ES therapy intervention or usual care control. All participants eligible for inclusion will be randomised on a 1:1 basis. Concealed random allocation will be conducted by a statistician using a computer-generated pseudo-random list with random permuted blocks of varying sizes. Allocation concealment will be ensured by the statistician preparing the randomisation codes in sealed envelopes that will only be opened by the researcher after the patient has been recruited and has completed all baseline measurements. Participants will be stratified into four groups (n=10):
No arm movement (Action Research Arm Test (ARAT)^21^ score=0) and cognitive impairment (Montreal Cognitive Assessment (MoCA)^22^ <26);No arm movement (ARAT^21^ score=0) but no cognitive impairment (MoCA^22^
>26);Some arm movement (ARAT^21^ score >1) and cognitive impairment (MoCA^22^ <26);Some arm movement (ARAT^21^ score >1) but no cognitive impairment (MoCA^22^
>26).

A minimisation technique will be applied during randomisation with minimisation on: age, sex, side of stroke and severity of arm weakness (as measured by the NIHSS^20^ arm subscore).

### Intervention treatment

Treatment with current controlled ES is delivered using a two channel constant current stimulation (maximum output 100 mA, pulse width 450 μs and a frequency between 40 and 60 Hz as per participant preference)^i^. The motor points for stimulation are selected to produce reciprocal flexion and extension through full range of movement.^23^ The initial assessment and treatment session with an NHS band 5 or above physiotherapist or occupational therapist will involve identification of the motor points for the forearm flexors and extensors, and placement of self-adhesive electrodes over these motor points. The current intensity will be increased to produce an alternating contraction of the flexors and extensors using a flex-hold-extend-hold pattern, ensuring that a pure movement is produced with no ulnar or radial deviation. The skin will be marked with a skin-safe marker pen to show the correct area to place the electrodes for future treatments and the ES device will be locked to the selected settings. A single stimulation and hold cycle will last 20 s and this will be cyclically repeated for 30 min after which the device can be removed.

Clinical staff will assist the patient to apply the electrode pads to the premarked motor points and switch on the device to the prestored treatment setting (this will take between 2 and 5 min) for subsequent treatments. The device will provide treatment without the need for a therapist to be present.

Prior to hospital discharge, the patient and/or nominated carer will be taught how to self-manage the treatment where possible. Treatment will continue twice a day, 5 days a week (Monday to Friday), for a total period of 3 months.

Modifications will not be made to the intervention. A participant may discontinue their allocated intervention or withdraw from the study for the following reasons: withdrawal of consent, or changes to their health status preventing their continued participation. Whenever possible, study participants will be retained in the trial to enable follow-up data collection and prevent missing data.

### Usual care control

Participants randomised to the control group will not receive ES therapy but will receive all usual care. ‘Usual care’ will include all the therapy interventions that are standard practice on the Nottingham Stroke Unit. As per national clinical guidelines,^2^ the application of ES to the upper limb is not standard practice. It is not possible to provide a placebo device without the possibility of it being easily identified as such. One reason is because movement is seen in the upper limb when the ES device is activated; furthermore, participants will be recruited and start treatment while on the hospital ward, so control and intervention participants may be in close proximity on the same wards as each other and would likely notice a difference between the intervention and placebo devices.

### Adherence to treatment

As part of the feasibility study data on adherence to the intervention treatment will be collected using two different methods. The ES devices have an internal memory function that will record data on usage. In addition, the study participants and/or their nominated carers will be asked to complete a patient diary to show the days and times that they have used the device. These data will be collected during the 3-month outcome assessment visit.

### Concomitant interventions during the trial

Participants enrolled on the ESCAPS trial cannot be enrolled in any other concomitant trials involving the application of experimental upper limb interventions that may impact trial outcomes.

### Blinding

It will be difficult to blind this study as the investigator and patient cannot be blinded during the procedure. However, an objective of this feasibility is to ascertain the most appropriate blinding procedure for the ensuing definitive trial.

The lead ward therapist will be informed of group allocation as they (or a nominated qualified therapist) will be providing the initial treatment. We will take every step to minimise allocation and outcome bias. Trial participants will not be blinded to group allocated because they will need to be informed as to whether they have been allocated to the intervention group receiving the ES therapy, or the control group who will not receive any ES therapy intervention.

The researcher responsible for the completion of outcome measures will not be blinded to group allocation as data on compliance will need to be collected via the use of participant diaries that will be collected at the 3-month follow-up assessment. This researcher will also have to record data on the number of ES treatments recorded (to measure home compliance) by the ES devices’ internal memory function (current intensity in mA and total time the device is used).

### Outcome measures

The primary outcomes relate to the feasibility outcomes of the study.
Feasibility of the trial design:
Recruitment rates: number/per cent of participants recruited within 72 h post-stroke; time post-stroke that participants received their first treatment;Recruitment strategy: number/per cent of patients screened, number/per cent eligible and approached, number/per cent who consented, number/per cent excluded after screening;Completion/attrition rates: number/per cent of participants who completed the intervention;Compliance/adherence to treatment protocol: number/per cent of participants who received ES twice a day, 5 days a week while in hospital, and number/per cent who continued with the treatment regime after discharge. Mean, minimum and maximum number of ES treatments that participants received during the 3-month intervention period;Consultee consent rates: number/per cent of patients unable to give informed consent, and number/per cent consented by a consultee, number of consultees who declined consent;Tolerability: number of participants who withdraw or decline intervention; records of interventions declined and why;Integrity of the study protocol: measured by examining how many participants are able to complete the study, number/per cent of missing data, and number/per cent of people who completed each of the outcome measures at 3-month, 6-month and 12-month follow-up, calculation of the cost of running the study; analysis of the qualitative interview and focus group data. The secondary outcomes relate to clinical outcome measures. Demographic characteristics (age, gender, ethnicity and socioeconomic status), stroke characteristics (date, type and side of stroke), cognitive status (MoCA^22^) and premorbid function state (Nottingham Extended ADL (NEADL)^24^) will be collected at baseline.

Participants will complete the following assessments at 0, 3, 6 and 12 months:
Neurological outcome (NIHSS^20^ score);Independence in daily activities (Barthel ADL Index score^25^ and modified Rankin Scale (mRS)^26^
^27^);Pain in the affected arm (Scale of Pain Intensity (SPIN)^28^);Muscle contractures/muscle activity (Biometrics EMG equipment);Arm function (ARAT^21^);Stroke-related quality of life (Stroke Specific Quality of Life Scale (SS-QOL))^29^;Health status (EuroQol-5D (EQ-5D)^30^);Patient resource use questionnaire;Carer strain (Caregiver Strain Index (CSI)^31^) will be completed by the participant's nominated carer.

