## Methods and analysis

### Study objectives

The primary objective of the study is to evaluate the feasibility of a RCT that will test the efficacy of delivering early, intensive ES to prevent poststroke complications (such as pain and contractures) to the paretic (weak) upper limb after stroke.

The objectives of this feasibility study therefore are to determine whether:
It is feasible to recruit within 72 h after stroke event, and to ascertain recruitment rates.Initiating ES therapy within 72 h after stroke event is appropriate.The ES regime proposed, that is, to start receiving ES on an acute stroke unit twice a day, 5 days a week and to continue with this schedule postdischarge for up to 3 months in total, is feasible, as measured by compliance, attrition and the qualitative work.Study the interaction between compliance and response to treatment in order to identify the optimum compliance.To determine preliminary health economic information surrounding the costs and benefits of the intervention.

We will also determine in this feasibility study what the most appropriate inclusion/exclusion criteria are; what the most sensitive and acceptable outcome measures are; the optimum method for single blinding and any barriers to compliance to the protocol from both the therapist and patient perspectives.

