### Participants

The study is set in Nottingham, England. Participants will be patients recruited from the Stroke Unit of the Nottingham University Hospitals NHS Foundation Trust within 72 h of stroke event.

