### Recruitment

For this feasibility study, we aim to recruit 40 participants over a period of 17 months from one centre (the Nottingham Stroke Unit at the Nottingham University Hospitals NHS Trust). The Clinical Research Network (CRN) stroke research officers will be notified by the clinical ward staff of newly admitted (within 72 h post-stroke) patients with stroke who meet the eligibility criteria. The clinical staff will have screened the patient against the eligibility criteria and those patients that meet the eligibility criteria will be informed of the study, and asked if they give voluntary consent. If the participant lacks capacity to consent for themselves, consent will be sought from an approved consultee according to the Mental Capacity Act. A stroke research officer will visit the patient on the ward to explain the study further and answer any questions.

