### Sample size

This is a feasibility study and therefore the sample size is determined by the number of participants that is feasible to study within the timescale of the project. Consecutive sampling will be used to recruit 40 participants. This will provide sufficient information to indicate feasibility. Outcome data will be utilised to inform a sample size calculation for the definitive trial by assessing variability and completeness of data.

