### Data analysis

Data will be statistically summarised/analysed using SPSS, and MathCad will be used to extract measures related to spasticity and contractures. Analyses will cover the following:
Total patients recruited within 72 h of stroke event; average length of time post-stroke when patients received first treatment.Total patients screened, eligible and approached, consented, and excluded after screening.Total patients who completed the intervention; number who completed 3-month, 6-month and 12-month follow-up assessments.Total participants receiving ES per protocol (PP); mean, minimum and maximum number of ES treatments received during 3-month intervention period; qualitative patient/carer interview data, and ES machine's memory which records number of sessions and duration.Total patients unable to give informed consent; number consented by consultee; number of consultees who declined.Recruitment and attrition rates, number of patients lost to follow-up and reasons.Quality of health economic data between assessment points especially 6–12 months regarding completeness. Cross referencing of data against medical records where possible. Sensitivity of the EQ-5D in measuring outcome. Combined cost and outcome analysis to determine potential cost-effectiveness of ES verses usual care.Thematic analysis will be used to identify themes representative of patient experience of treatment, and the experience of carers with the application of the ES device.

As the sample size is small and a method of minimisation is used, we propose to estimate effect size (using the Cohen's d and the 95% CI) for the main study measures that are interval level data. The OR (and the 95% CI) will be estimated when data are dichotomous. When measures are ordinal, nominal relative risk ratios will be used to present all forms of adverse events.

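### The percentage of participants recruited within 72 h is 100% by construction, no count of ES started within 72 h is named, and adherence data have only one stated collection point, at 3 months

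*Protocol article*

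**What the plan says.** All references are to the protocol article.

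- **Recruitment outcome.** Outcome measures lists, among the primary outcomes, "Recruitment rates: number/per cent of participants recruited within 72 h post-stroke; time post-stroke that participants received their first treatment". The next item there is a flow of patients screened, eligible and approached, consented, and excluded.
- **Who is a participant.** Participants states: "Participants will be patients recruited from the Stroke Unit of the Nottingham University Hospitals NHS Foundation Trust within 72 h of stroke event". Under Recruitment, the research officers "will be notified by the clinical ward staff of newly admitted (within 72 h post-stroke) patients with stroke who meet the eligibility criteria". Neither Inclusion criteria nor the criteria in Table 1 contain a 72 h item.
- **Early start.** The Introduction argues that treatment needs to begin inside 72 h, and Study objectives asks whether "Initiating ES therapy within 72 h after stroke event is appropriate". The summary named in Data analysis is the "average length of time post-stroke when patients received first treatment".
- **Adherence.** Outcome measures asks for separate figures for the full schedule in hospital and for continuation after discharge. Adherence to treatment names two sources, the device's internal memory and a diary of days and times, and adds: "These data will be collected during the 3-month outcome assessment visit". Blinding says the researcher records the number of treatments from the device memory and describes its content as "current intensity in mA and total time the device is used". Data analysis describes the memory as holding number of sessions and duration.

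**The concern.** A feasibility trial is judged by what its feasibility outcomes can show, and three of them are weaker than they need to be.

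First, a percentage whose denominator already requires the numerator's condition cannot vary. The first objective asks whether recruitment inside 72 h is feasible. The informative quantity is how many otherwise suitable patients could not be reached in time, and no stated outcome gives it.

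Second, recruitment inside 72 h does not ensure treatment inside 72 h. Consent, baseline measures and randomisation come first, and a therapist must then locate the motor points. An average time does not show how many participants met the limit.

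Third, with one stated collection point at 3 months, adherence data may be missing for those who die or withdraw before it. If the device holds only totals, the split between hospital and home rests on the self-reported diary. The definitive trial's design will draw on all three figures.

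**Working it through.** **Inputs.** From the article: target of 40 (Sample size: "Consecutive sampling will be used to recruit 40 participants"); 1:1 allocation, so about 20 in the ES arm (Study design); two sessions a day, 5 days a week, for 3 months (Intervention treatment). Assumed: 3 months taken as 13 weeks; the means and SDs of time to first ES; the lengths of hospital stay; the cumulative session total. The target of 40 was set by what is practicable, so there is no power figure to reproduce.

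**Step 1: the 72 h recruitment percentage.** Let R be the number recruited under the stated rule. Every one of the R is within 72 h, so the outcome is R/R = 40/40 = 100%. The nominal exact 95% interval, 91.2% to 100%, has no feasibility meaning because the figure could not have been anything else. Let M be the number of otherwise eligible admissions missed because 72 h had passed. M does not enter R/R, so the outcome is the same whether M is zero or large. The screening flow would reveal M only if those patients enter the screened count and lateness is recorded as a reason. The article states neither.

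**Step 2: average time against share treated in time.** For a lognormal with mean m and standard deviation s, put σ² = ln(1 + (s/m)²) and μ = ln(m) − σ²/2. The share at or below 72 h is Φ((ln 72 − μ)/σ).

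| Assumed mean | SD 6 h | SD 12 h | SD 24 h | SD 36 h |
|---|---|---|---|---|
| 60 h | 97% | 85% | 75% | 73% |
| 66 h | 84% | 72% | 66% | 67% |
| 72 h | 52% | 53% | 56% | 59% |
| 78 h | 16% | 33% | 45% | 52% |

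The same average is compatible with quite different shares. The individual times are collected, so the count needs no new data. With 20 in the ES arm, exact (Clopper-Pearson) 95% intervals would be:

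- 10/20 = 50%: 27.2% to 72.8%
- 14/20 = 70%: 45.7% to 88.1%
- 18/20 = 90%: 68.3% to 98.8%
- 20/20 = 100%: 83.2% to 100%

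These are wide but informative.

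**Step 3: what a cumulative device total can show.** Planned sessions are 2 × 5 × 13 = 130. Suppose the device shows 104 in total and nothing is dated. With H sessions due in hospital, the in-hospital share lies between max(0, 104 − (130 − H))/H and min(H, 104)/H.

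- Stay of 2 weeks, H = 20: from max(0, 104 − 110)/20 = 0% to 20/20 = 100%.
- Stay of 4 weeks, H = 40: from (104 − 90)/40 = 35% to 40/40 = 100%.

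A total alone therefore does not give the split that Outcome measures asks for. A dated diary or a time-stamped memory can.

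**Step 4: direction of any loss of adherence data.** Purely as illustration, let those who complete average 100 sessions and those who stop early average 20, and let every early stopper's device and diary be lost. With 10%, 20% or 30% stopping early, the true means are 0.9 × 100 + 0.1 × 20 = 92, 0.8 × 100 + 0.2 × 20 = 84 and 0.7 × 100 + 0.3 × 20 = 76. The reported mean is 100 in each case, which is 9%, 19% or 32% too high. None of these inputs comes from the article, so they show direction only.

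**The case against.** The strongest reply is that the article already contains most of what is needed, and much of this reply stands.

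- The recruitment objective does not rest on the 72 h percentage alone, because the screening-to-consent flow is also a primary outcome. Clinical staff screen before notification, so late arrivals might be counted there. This is fair, but no count of patients missed because of the window is named.
- Time to first treatment is itself a primary outcome, so the share within 72 h is derivable. The choice of median, interval or threshold is often left to an analysis plan. This too is fair: the gap is an unnamed summary, not missing data.
- The diary records days and times, so it can separate hospital from home. Both Blinding and Data analysis mention a number of treatments or sessions, and the memory may be time-stamped. The article does not say, and the diary remains self-report.
- Someone who stops ES but stays in follow-up can still be read at 3 months. The article intends to retain participants where possible and also records declined interventions and withdrawals. Only those who die or withdraw before the visit are clearly at risk of having no data.

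A reader might infer that the outcomes cannot answer their objectives, or that the trial could declare 100% success. The documents do not support this: the flow and the individual times are collected, and no success threshold is set. A reader might also infer that 72 h is a listed eligibility criterion. It is not; it comes from the definition of participants and the notification route.

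**Conclusion.** The point holds in a limited form. One primary percentage is uninformative: it is 100% if the stated recruitment route is followed. The early-start objective is summarised by an average that does not fix the share treated in time; at an assumed mean of 66 h that share runs from 66% to 84%. The single stated 3-month collection may leave adherence unknown for participants lost earlier. Two differing descriptions of the device memory leave it unclear whether the hospital and home figures can be checked against anything but the diary.

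It does not follow that adherence will be overstated. That needs early stoppers' data to be lost, and the size depends on rates and session counts for which the article gives no source. The step 2 shares likewise depend on the assumed lognormal shape, means and SDs, and the step 3 bounds on the assumed stay and total. The 100% result depends only on the article's own text. These are improvements worth making; they do not invalidate the design.

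**What to change.** 1. **Recruitment.** Take as denominator all stroke-unit admissions meeting the other criteria, whatever the time since stroke. Report the number missed because 72 h had passed, alongside the existing flow.
2. **Early start.** Add the number and percentage of the ES arm whose first session fell within 72 h, with an exact 95% CI, and give the median and interquartile range of time to first session.
3. **Adherence.** Reconcile the descriptions of the device memory in Blinding and Data analysis, and state whether entries are dated. Collect device memory and diary at hospital discharge and at withdrawal or device return, as well as at 3 months. Report adherence for everyone randomised to ES, showing how many have no read-out.

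The cost is one further item in the screening record, one extra read-out per ES participant, and a headline percentage that will probably look less favourable. Item 2 needs no new data. None of the changes alters the treatment.

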### Data collection methods

Following recruitment to the trial, a stroke researcher will visit the participant on the ward to obtain the baseline measurements. In cases where it is not possible to obtain all the outcome measurement data from the patient or the medical records, for the BI, NEADL, mRS, resource use questionnaire, the researcher will obtain by proxy data from the next of kin. A stroke researcher will visit the participant at their place of discharge to complete the 3-month, 6-month and 12-month follow-up assessments.

### Sample size

This is a feasibility study and therefore the sample size is determined by the number of participants that is feasible to study within the timescale of the project. Consecutive sampling will be used to recruit 40 participants. This will provide sufficient information to indicate feasibility. Outcome data will be utilised to inform a sample size calculation for the definitive trial by assessing variability and completeness of data.

